### Intervention

The RM protocol is based on the ‘stages of change’ model [19]. In this model change is considered as a process directed towards progress through a series of stages (precontemplation, contemplation, preparation, action and maintenance). The education and counselling of an individual persons’ needs depend on the stage he or she is in. People in the precontemplation and contemplation stage require information about the advances of a healthy lifestyle. People in the preparation stage are already aware of the advantages and disadvantages of a healthy lifestyle and require counselling and guidance to improve their ability to change their lifestyle. In the action stage, people do require tips and strategies for making the actual change. In the maintenance stage people may need additional guidance and feedback to stimulate them in maintaining their changed behaviour and to prevent relapse.

The first section of the protocol focuses on case finding and testing (Figure 2). The general practitioner is responsible for assessing subjects’ individual risk to develop T2DM. When someone is diagnosed with IFG, the second section of the RM is applied (Figure 3). This section of the protocol focuses on coaching the individual person to a healthy lifestyle. The practice nurse tries to get insight into the motivational situation of the participant. Based on this insight, three to four extra consultations spread over a one year period are carried out. During these consultations the practice nurse gives advice and teaches concrete and applicable skills in order to increase the level of physical activity and healthy dietary habits. If necessary, participants are referred to a dietician, physiotherapist, lifestyle programs and/or local sports activities. The practice nurse applies motivational interviewing techniques to determine someone’s motivational situation and to help a person to change his or her behaviour based on the model of stages of change [19,20]. After one year participants receive care as usual.

**Figure 2 F2:**
[figure not shown]
Case finding and testing (first section of the RM protocol).

**Figure 3 F3:**
[figure not shown]
Counselling schedule (second section of the RM protocol).

After the initial development of the RM protocol it has been piloted on practical feasibility in different small scale pilot studies. The results of these pilots were used to improve the protocol.

### Care as usual

Care as usual for those with IFG means a yearly check on diabetes-related symptoms and blood glucose levels according to the T2DM guideline of the Dutch College of General Practitioners [7].

#### Outcomes

The primary outcome measure in this study is change in Body Mass Index (BMI). Secondary outcome measurements are waist circumference, total and saturated fat intake, physical activity, systolic blood pressure, blood glucose, total cholesterol, triglycerides and the behaviour determinants risk perception, perceived knowledge, motivation, attitude, self efficacy and social norm.

#### Measurements

##### Medical records

The practice nurse measures body weight, blood pressure and waist circumference. Fasting plasma glucose levels, HbA1c, and serum lipids are determined in regional laboratories. Information on family history of diabetes, history of elevated blood glucose, ethnicity, other cardiovascular risk factors and comorbidity are recorded by the practice nurse. Furthermore, the practice nurse is responsible for collecting and reporting this data at three moments in time: just after the diagnosis (t0) and during the yearly follow-up consultations (t1 and t2).

### Questionnaires

All participants are asked to complete a questionnaire at three different time points. The questionnaire is handed over by the practice nurse to the participants right after the diagnosis (t0) and after the yearly follow-up consultations (t1 and t2). Participants send the questionnaire directly to the researchers. The questionnaire at t0 comprises general background information on demographic characteristics (including sex, age, ethnicity, education, household composition and occupational situation). The questionnaires at t0, t1 and t2 comprise general health (including perceived health, smoking behaviour, and alcohol consumption), dietary habits (including total and saturated fat intake) [21] and physical activity (including minutes of light, moderate and intense physical activity per week) [22]. Furthermore, promoting and inhibiting factors for compliance are asked (including appreciation of care regarding to their high risk on diabetes, self-efficacy regarding lifestyle change, attitude towards lifestyle change and social norm on healthy living).

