## Methods

### Study design

A clustered randomized controlled trial is carried out to study the feasibility and (cost-)effectiveness of the RM. Randomization takes place at the level of the general practices. The subjects in the intervention group are treated according to the RM. Persons in the control group receive care as usual, including one consultation each year, according to the T2DM guideline of the Dutch College of General Practitioners [7]. A baseline measurement takes place just after the diagnosis of IFG and just before the start of the intervention. Outcome measurements are performed one year after the diagnosis (t1, 1-year follow-up) and two years after the diagnosis (t2, 2-year follow up) (Figure 1).

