### Training

The practice nurse carries out the intervention with support of the general practitioner, if necessary. Besides carrying out the RM, the practice nurses are responsible for the data collection. Prior to the start of the study, all practice nurses of the intervention group are trained to support them in applying the protocol. Additionally they are trained in techniques of motivational interviewing.

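### At t1, and more weakly at t2, the self-report questionnaire is issued after the yearly visit, which in the intervention arm is with the coaching nurse; it could be issued before the visit in both arms

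*Protocol article*

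**What the plan says.** The Questionnaires section of the protocol article covers both arms: "All participants are asked to complete a questionnaire at three different time points". On the hand-over it states: "The questionnaire is handed over by the practice nurse to the participants right after the diagnosis (t0) and after the yearly follow-up consultations (t1 and"; its last words extend this to t2. On return: "Participants send the questionnaire directly to the researchers". It does not say when, after receiving the form, the participant fills it in.

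The Training section describes the nurse's two roles: "The practice nurse carries out the intervention with support of the general practitioner, if necessary" and "Besides carrying out the RM, the practice nurses are responsible for the data collection". Of the intervention-group nurses it adds: "Additionally they are trained in techniques of motivational interviewing". No such training is described for control nurses.

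The Intervention section places three to four extra coaching consultations within one year and returns participants to usual care after that. For controls, Study design provides one consultation a year, and the Care as usual section says: "Care as usual for those with IFG means a yearly check on diabetes-related symptoms and blood glucose levels".

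The Outcomes section lists fat intake, physical activity and six behaviour determinants as secondary outcomes. The Abstract assigns activity, food intake and their determinants to the questionnaire.

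**The concern.** The order is a stated choice: consultation first, form second. The outcomes on the form are what the coaching tries to change, and the participant reports them. In one arm, the person seen immediately before the form is issued has coached the participant on diet and activity for a year. In the other arm it is a nurse giving a yearly check. A participant who has just talked with the coach may describe habits, motivation or self-efficacy more favourably than the same participant would have done before the visit. The determinants are the most exposed, since motivational interviewing works on them directly.

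If this happened more in one arm, part of a between-arm difference in these outcomes would reflect the occasion of measurement and not the preceding year. The physical activity result also matters beyond its own test: the Cost-effectiveness section relates costs to the effects on BMI and on physical activity.

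**Working it through.** The plan gives no figure for this effect, so the main check compares what the article says at each time point.

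**Contact before the form**

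| | Intervention arm | Control arm |
|---|---|---|
| t1 | Yearly follow-up visit with the nurse who coached during the year (Training, Intervention) | Yearly visit under usual care (Study design, Care as usual) |
| t2 | Yearly visit; participant back on usual care for about a year (Intervention) | Yearly visit under usual care |

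- **t1:** the nurse's training, the coaching relationship and the year just completed all differ by arm. The content of the visit is not described, and the article does not say it is one of the extra coaching sessions. That it differs by arm is therefore a plausible inference, not a stated fact.
- **t2:** the care is nominally the same. Only the nurse's training and the earlier relationship differ.
- **t0:** Study design says "A baseline measurement takes place just after the diagnosis of IFG and just before the start of the intervention", and Questionnaires places hand-over right after the diagnosis. These agree, so there is no finding at baseline.

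**Which outcomes are exposed.** Under Measurements, the nurse measures weight, waist and blood pressure, and laboratories determine glucose and lipids. BMI is therefore not exposed by this route. Activity, fat intake and the determinants are.

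**The plan's only sample-size figure**, 120 per group, concerns BMI. Inputs from the Sample size calculation: difference 0.5, SD 1.37, two-sided alpha 0.05, power 80%.

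n per arm = 2 × (1.37 × (1.960 + 0.842) / 0.5)² = 117.85, so 118 without clustering. With ICC 0.011 and an assumed 2 participants per practice, 117.85 × (1 + 1 × 0.011) gives 120. The stated figure reproduces and does not depend on when the form is issued.

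**Illustration only.** Suppose the visit shifts a score by d SD more in the intervention arm, with no true effect. With 120 per arm and no clustering, the mean of the test statistic is d / √(2/120). With an assumed 10 participants per practice, the design effect is 1 + 9 × 0.011 = 1.099 and the mean is d / √(2 × 1.099/120).

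| Assumed d | Mean Z, no clustering | P(two-sided p < 0.05) | Mean Z, design effect 1.099 | P(two-sided p < 0.05) |
|---|---|---|---|---|
| 0 | 0 | 5% | 0 | 5% |
| 0.1 | 0.77 | 12% | 0.74 | 11% |
| 0.2 | 1.55 | 34% | 1.48 | 32% |
| 0.3 | 2.32 | 64% | 2.22 | 60% |

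No value of d above zero is supported by the documents. The table shows only that a small shift would matter if it existed.

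**The case against.** The case on the other side is substantial.

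- **The procedure is the same in both arms.** True, but the same hand-over after a different exposure does not remove differential reporting.
- **The visit is not shown to differ by arm.** A reader might infer from the order that both follow-up forms follow a different consultation in each arm. The article does not support that. At t2 both arms are on usual care, and at t1 the content of the visit is not described. This stands, and limits the point to a plausible difference at t1 and a weak one at t2.
- **Answers are not shown to be given on the spot.** A reader might take the form as completed straight after the visit. The article gives only the time of hand-over. Direct return also keeps the answers from the coach, which reduces the pressure to please. It does not undo influence before completion.
- **Harm is not demonstrated.** A reader might conclude that the order must produce a between-arm difference. Nothing in the article shows this, and the shifts in the table are assumed.
- **Baseline.** A reader might suspect that t0 forms are completed after coaching has begun. The two passages on baseline agree, and how completion is enforced is operational detail that an article leaves to the full protocol.
- **Reversing the order leaves most reporting bias in place.** Participants coached for a year know what they were coached on, whichever day they answer. This stands: only the influence of the visit is removed.
- **There is a reason to issue the form afterwards.** Process evaluation uses the questionnaires to ask about experiences with care and referrals. Wording those items to cover the preceding year meets this.

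**Conclusion.** The point holds in a limited form. The article fixes the issue of the form after the yearly consultation. In the intervention arm, that consultation is with an unblinded nurse who did the coaching and is trained in motivational interviewing. Self-reported secondary outcomes at t1 may therefore be influenced by a contact that plausibly differs by arm. At t2 the same argument rests only on the nurse's training and the past relationship.

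The direction one would expect favours the intervention, but the documents establish neither direction nor size. The conclusion assumes that the t1 visit differs in practice between arms, and that some participants answer soon enough afterwards for it to matter. The primary comparison on BMI is untouched by this route. What is at stake is the interpretation of activity, fat intake and the determinants, and the activity input to the cost-effectiveness model. The change is worth making because it costs little, not because a bias has been demonstrated.

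**What to change.** 1. In both arms, issue the t1 and t2 questionnaires before the yearly consultation, with an instruction to complete them beforehand. Keep the direct return to the researchers.
2. Add a completion-date field to the form.
3. Word the few items on experience with care and referrals as questions about the preceding year, so that they do not need to follow the visit.
4. When reporting the self-reported outcomes, acknowledge that participants and coaches were unblinded and that reporting bias from a year of coaching remains.

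Forms completed late should stay in the analysis. Leaving them out would select participants on behaviour after randomisation, which may itself differ by arm.

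The cost is a changed instruction, one date field, slightly more mailing and a reminder for participants whose form is not in by the visit. Sample size, the primary analysis and care in either arm are unaffected.

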### Process evaluation

A process evaluation is carried out to gather information about the care given in the intervention and control group. This evaluation consists of registration forms, questions in the questionnaire of the intervention group at t1 and t2, and face-to-face interviews with the practice nurses responsible for the study. Time spent on the intervention is recorded on registration forms. In the questionnaires participants in both groups are asked about their experiences with the offered care and referrals. In each participating general practice a face-to-face interview with the practice nurse responsible for the study takes place. During these interviews information is gathered about the inclusion of participants, the implementation of the care, the education and motivation of the practice nurses, the number of referrals, experienced motivation and treatment possibilities of the participants. In the intervention group practice nurse are asked about the perceived effect of the RM and advice for further implementation of the RM.

#### Sample size calculation

The sample size calculation is estimated based on BMI with the objective to detect a decrease in BMI of 0.5 in the intervention group. In the SLIM study, the standard error of the mean in change in BMI was 0.2 kg/m2 and the standard deviation 1.37 [16]. The SLIM study has a comparable population to this study, so it is assumed that the standard error and standard deviations are also comparable. To adjust for clusters, an intra-cluster correlation of 0.011 is used [23]. Furthermore, a power of 80% and a two-sided alpha of 0.05 is used. Based on these assumptions, 120 people in each group are needed.

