**Methods/Design:**

A cluster randomised clinical trial is performed, with randomisation at the level of the general practices. Both opportunistic screening and active case finding took place among clients with high risk factors for diabetes. After IFG is diagnosed, motivated people in the intervention practices receive 3–4 consultations by the practice nurse within one year. During these consultations they are coached to increase the level of physical activity and healthy dietary habits. If necessary, participants are referred to a dietician, physiotherapist, lifestyle programs and/or local sports activities. The control group receives care as usual. The primary outcome measure in this study is change in Body Mass Index (BMI). Secondary outcome measures are waist circumference, physical activity, total and saturated fat intake, systolic blood pressure, blood glucose, total cholesterol, HDL cholesterol, triglycerides and behaviour determinants like risk perception, perceived knowledge and motivation. Based on a sample size calculation 120 people in each group are needed. Measurements are performed at baseline, and after one (post-intervention) and two years follow up. Anthropometrics and biochemical parameters are assessed in the practices and physical activity, food intake and their determinants by a validated questionnaire. The cost-effectiveness is estimated by using the Chronic Disease Model (CDM). Feasibility will be tested by interviews among health care professionals.

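### The stated 120 per group gives 80% power at an ICC of 0.011 only with about 2 to 3 analysed participants per randomised cluster, and no cluster size is stated

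*Protocol article*

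**What the plan says.** The section on sample size in the protocol article bases the calculation on BMI, with "the objective to detect a decrease in BMI of 0.5 in the intervention group". The variability comes from an earlier Dutch lifestyle study (SLIM), in which "the standard error of the mean in change in BMI was 0.2 kg/m2 and the standard deviation 1.37". On clustering it says: "To adjust for clusters, an intra-cluster correlation of 0.011 is used [23". The error rates are given as "a power of 80% and a two-sided alpha of 0.05 is used", and the paragraph ends: "Based on these assumptions, 120 people in each group are needed". The abstract repeats the figure of 120.

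The section on randomisation makes the general practice the unit, and puts practices that share a health centre into the same arm. The section on analysis specifies multilevel models and adjustment for baseline values. The article does not state the number of practices, the number of participants per practice or health centre, or the design effect.

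**The concern.** An ICC changes a sample size only through a cluster size: the design effect is 1 + (m − 1) × ICC for m participants per cluster. The paragraph gives the ICC but not m, so the reader can only work back from the result. That result is almost the number that an individually randomised trial would need, so the adjustment described in the text can have added very little.

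What is at stake is the 80% power claim for the primary outcome. The discussion section says that the results will inform policy on lifestyle programmes in Dutch primary care. A null finding on BMI would be read against that claim. If clusters are of ordinary size, the trial has less power than stated, and an absence of effect could be over-read.

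**Working it through.** **Inputs** (all from the sample size paragraph): difference δ = 0.5 kg/m², SD of change σ = 1.37, ICC ρ = 0.011, two-sided alpha 0.05 (z = 1.95996), power 80% (z = 0.84162). The SD and standard error agree with each other: (1.37/0.2)² ≈ 47 people. **Assumed**, because not stated: m analysed participants per randomised cluster, equal cluster sizes, everyone analysed.

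**Step 1: reproduce the figure without clustering.**

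n = 2(1.95996 + 0.84162)² × 1.37² / 0.5² = 117.85, so 118 per group. The t-based calculation gives 119. A single-group change would need half of 117.85, which is 58.9 or 59 people, so the figure of 120 comes from a between-group comparison.

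**Step 2: the design effect that 120 can hold.**

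120 / 117.85 = 1.018. Setting 1 + (m − 1) × 0.011 = 1.018 (unrounded 1.0182) gives m = 1 + 0.0182/0.011 ≈ 2.66. With 240 people that is 240/2.66 ≈ 90 clusters, or about 45 per arm.

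**Step 3: check small clusters with the ICC applied.**

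- m = 2: 117.85 × 1.011 = 119.1, so 120 per group; power at 120 is 80.3%.
- m = 3: 117.85 × 1.022 = 120.4, so 121 per group; power at 120 is 79.9%.

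The stated figure therefore does reproduce with the ICC applied, but only at about this cluster size.

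**Step 4: larger clusters.**

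Required n = 117.85 × DE, with DE = 1 + (m − 1) × 0.011. Power at 120 per group = Φ(0.5 / √(2 × 1.37² × DE / 120) − 1.96). The last column uses a noncentral t with 2k − 2 degrees of freedom, where k = 120/m is the number of clusters per arm.

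| m | DE | n per group needed | Power at 120, normal | Power at 120, cluster df |
|---|---|---|---|---|
| 5 | 1.044 | 124 (123.04) | 79.0% | 77.3% |
| 10 | 1.099 | 130 | 76.9% | 73.2% |
| 20 | 1.209 | 143 | 72.9% | 64.1% |

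**Step 5: difference detectable with 80% power at 120 per group** (normal approximation).

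δ = 2.80158 × √(2 × 1.37² × DE / 120). At m = 10: 2.80158 × √0.03438 = 0.519. At m = 20: 2.80158 × √0.03782 = 0.545.

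**The case against.** **The cluster size is unknown, so no shortfall is proven.** This stands as a limit. A reader might infer that the ICC was never applied and that 80% power is definitely not reached. The article does not support either statement: at 2 to 3 per cluster, 120 is consistent with the ICC having been applied and with power of about 80%. Joint allocation within health centres, and case finding from the patient files in the practices, make such small clusters hard to credit, but they do not exclude them.

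**The planned analysis is more efficient than the calculation.** The section on analysis adjusts for baseline, which multiplies the variance of change by (1 + r)/2, where r is the correlation between baseline and follow-up BMI. The article gives no SD for BMI itself. If it is assumed to be 3 to 4 kg/m², then 1.37² = 2 × SD² × (1 − r) gives r of about 0.90 to 0.94 and a factor of 0.948 to 0.971. The tolerable design effect becomes 1.074 to 1.049, or about 7.7 to 5.5 participants per cluster. Power would then be 80 to 81% at m = 5, 78 to 79% at m = 10 and 74 to 75% at m = 20 (normal approximation, same ICC). This is a fair offset, but a partial one, and the paragraph does not claim it.

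**Loss to follow-up.** A reader might add that nothing is allowed for dropout over two years. That is not a finding here. A condensed article may leave a recruitment allowance to the full protocol, and 120 can be read as the number analysed.

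**The wording of the target.** A reader might take the reference to the intervention group as a single-group target. The figure reproduces only as a between-group difference, and the section on analysis compares groups, so this is a matter of wording.

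**Inference is protected.** Multilevel models are specified, so this paragraph does not affect the type I error or the effect estimate. That is correct, and it keeps the point to one of stated power.

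**Conclusion.** The point holds in a limited form. The stated combination of 120 per group, ICC 0.011 and 80% power is consistent only with about 2 to 3 analysed participants per randomised cluster, or about 90 clusters. The article neither states nor justifies such a cluster size, and its rule of keeping health centres together points towards larger clusters.

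The loss of power is modest with small clusters and material with larger ones. It is about one point at 5 per cluster, three at 10 and seven at 20 on the normal approximation, and about three, seven and sixteen with cluster-based degrees of freedom. These figures rest on assumed, equal cluster sizes, 120 analysed per group and no gain from baseline adjustment. This is a correction to a stated figure and does not threaten the validity of the analysis.

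**What to change.** In the sample size paragraph:

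1. State the expected number of analysed participants per randomised cluster, where the cluster is the health centre if its practices are allocated together and the practice otherwise.
2. Apply 1 + (m − 1) × 0.011 with that m and show the design effect.
3. Replace 80% by the power that 120 analysed per group then gives, or keep 80% and give the detectable difference (about 0.52 kg/m² at 10 per cluster, just under 0.55 at 20). If a gain from baseline adjustment is claimed, state the correlation assumed.
4. While the paragraph is open, describe the 0.5 as a between-group difference in BMI change.

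The cost is the rewording of one paragraph. No extra enrolment is needed. The only downside is that the stated power may become slightly less favourable.
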